*This document is an English translation of the 2nd modified trial protocol submitted to the Central Denmark Region's Ethics Committee on December 17, 2015.*

## Remote Ischemic Preconditioning in Head and Neck Cancer Reconstruction - A Randomized Controlled Trial

### Aim

The aim of the trial is to investigate if remote ischemic preconditioning improves the outcome of microsurgical reconstruction.

### Literature review

Overview of systematic literature review performed in PubMed/MEDLINE:

| Search terms (April 7, 2015)                                                | Identified references: |
|------------------------------------------------------------------------------------|-------------------------------|
| "Ischemic Preconditioning"[Mesh] AND "Hemostasis"[Mesh]                            | 20                            |
| "Blood Coagulation"[Mesh] AND "Ischemic Preconditioning"[Mesh]                     | 4                             |
| "Ischemic Preconditioning"[Mesh] AND "Fibrinolysis"[Mesh]                          | 2                             |
| "Thrombosis"[Mesh] AND "Ischemic Preconditioning"[Mesh]                            | 20                            |
| ischemic preconditioning coagulation                                               | 35                            |
| "Surgical Flaps"[Mesh] AND "Ischemic Preconditioning"[Mesh]                        | 78                            |
| "Surgical Flaps"[Mesh] AND "Ischemic Preconditioning"[Mesh] AND "Hemostasis"[Mesh] | 0                             |
| "Surgical Flaps"[Mesh] AND "Ischemic Preconditioning"[Mesh] AND "Thrombosis"[Mesh] | 0                             |

Additional literature was identified through review of reference lists from relevant publications.

### Background

In microsurgical reconstruction, the patient's own tissue is applied for reconstruction of defects following tumor resection or trauma. Blocks of tissue are harvested from a donor site and transferred to the defect, where the blood supply is restored by microvascular anastomoses under the operating microscope. These tissue blocks are termed 'free flaps'. For example, the fibula bone with a skin paddle from the lower leg is applied for reconstruction of the jawbone and oral cavity following resection of oral cancer.

Thrombosis to the vascular anastomoses and microcirculatory intravascular thrombosis are the main reasons for total flap necrosis. Total flap necrosis occurs in 1-9 per cent of cases with devastating consequences for the patient [1-3]. Therefore, research aimed at reducing the risk of thrombosis in free flap reconstruction is essential.

The surgical procedure results in a hypercoagulable state, endothelial dysfunction, and altered blood flow in the patient's circulation during free flap reconstruction. It is well known, that oncologic patients are in a hypercoagulable state with an increased risk of thrombosis [4]. Ischemia-reperfusion injury to the flap, and the suture line of the anastomoses, are the main reasons for endothelial dysfunction in the flap. Furthermore, stasis and hypoxia in the patient's circulation contribute to endothelial dysfunction. These changes in the coagulation system result in an increased risk of thrombosis and have major impact on the outcome of free flap reconstruction.

Ischemic preconditioning, where brief periods of ischemia and reperfusion are induced prior to prolonged ischemia, has been shown to attenuate ischemia-reperfusion injury of organs subject to acute ischemia [5]. Ischemic preconditioning can either be applied locally on the organ prior to ischemia, or anatomically remote by ischemic preconditioning of tissue separate from the target organ, termed remote ischemic preconditioning [6]. Furthermore, remote ischemic perconditioning, applied during target organ ischemia, and remote ischemic postconditioning, applied at reperfusion of the ischemic organ, have been described as methods to reduce ischemia-reperfusion injury [7-8]. Randomized controlled trials with remote ischemic perconditioning as an adjunct to revascularization in patients with myocardial infarction or ischemic stroke have shown promising results [9-10].

The mechanism behind remote ischemic conditioning is unknown, but the research has focused on a humoral response or a neurogenic response [11-13]. Furthermore, effects involving the immune system and coagulation system have been investigated [14-16]. Ischemic preconditioning and remote ischemic preconditioning of experimental free flaps have been shown to increase flap survival and attenuate ischemia-reperfusion injury [13,17-20]. However, just one clinical case series with six preconditioned abdominal flaps for breast reconstruction has been published. And two clinical studies with healthy subjects have shown, that remote ischemic conditioning improves the cutaneous microcirculation at a free flap donor site [21-23]. Hence, no randomized controlled trials have been conducted to show the efficacy of remote ischemic conditioning in free flap reconstruction.

### **Study aims**

- 1) To investigate if remote ischemic preconditioning attenuates platelet aggregation in head and neck cancer patients undergoing microsurgical reconstruction.
- 2) To investigate if remote ischemic preconditioning induces fibrinolysis in head and neck cancer patients undergoing microsurgical reconstruction.

### **Hypotheses**

- 1) Remote ischemic preconditioning attenuates platelet aggregation.
- 2) Remote ischemic preconditioning increases fibrinolysis.

## **Study participants, methods and materials**

Design: Randomized controlled trial.

Study intervention: Included patients will be randomized in the operating room after induction of general anesthesia to remote ischemic preconditioning or no remote ischemic preconditioning (sham). Patients are blinded to the study intervention. Remote ischemic preconditioning will be carried out by upper extremity ischemia using an inflatable tourniquet. Four cycles of 5 min ischemia followed by 5 min of reperfusion will be administered. In patients randomized to sham, the tourniquet will be applied to the patient, but not inflated.

### Eligibility:

Inclusion criteria:

- At least 18 years of age.
- Ability to give informed consent.
- Will undergo resection of a malignant tumor in the head and neck region immediately followed by microsurgical reconstruction with a single free flap at the Department of Plastic Surgery, AUH.

Exclusion criteria: Arterial or venous thromboembolism in the previous three months.

### Outcomes:

Biochemical data:

- Primary hemostasis: Platelet count and platelet aggregation (Multiplate®).
- Secondary hemostasis: aPTT, INR, antithrombin, and thrombin-antithrombin complex.
- Fibrinolysis: Fibrin clot lysis, fibrin d-dimer, prothrombin fragment 1+2, plasminogen activator inhibitor-1, tissue-plasminogen activator, plasminogen, and thrombin-activatable fibrinolysis inhibitor.
- Global hemostasis: Thrombin generation.
- Systemic inflammation: C-reactive protein, leukocytes, fibrinogen, interleukin-6, and von Willebrand factor (antigen).

Blood samples will be drawn at:

1. Just before induction of general anesthesia.
2. At randomization (intraoperatively).
3. 3 h after RIPC/sham.
4. 6 h after RIPC/sham.
5. 06:30 AM on the 1st postoperative day.

Clinical data:

- Previous treatment for head and neck cancer
- Co-morbidities
- Medication
- Course of hospitalization
- Re-operations
- Morbidity and mortality

Follow-up for clinical data is 30 days postoperatively. Data will be collected from review of patients' electronic medical records and postoperative visits to the Plastic Surgery Clinic, AUH.

### **Obtaining informed consent**

Potential study participants will be encountered in the multidisciplinary Head and Neck Cancer Clinic, AUH, where newly referred head and neck cancer patients are evaluated for surgery by head and neck surgeons, plastic surgeons, maxillofacial surgeons, and oncologists. Patients who are scheduled for surgery, and who meet the inclusion criteria, will receive verbal and written information about the clinical trial from [name] [name], [name] [name], [name] [name], or M.D./Ph.D. student [name]. This conversation will take place in a private clinic room with no interruptions, and the patient's companions are encouraged to join the conversation.

Informed consent for trial participation will either be obtained immediately, or the patient is offered time for deliberation until the day of admission before surgery. Under normal circumstances the patient will be scheduled for surgery within 14 days from their first visit to the Head and Neck Cancer Clinic.

### **Biobanks**

Trial biobank: From each blood sample, 12 mL blood will be analyzed immediately, and the remaining blood will be stored as plasma at -80 degrees Celsius for batch analyses. These batch analyses will be performed before the project end date on January 31, 2020. This biobank will be established at the Department of Clinical Biochemistry, AUH.

Biobank for future research: Consent will be obtained from study participants for collection of extra blood at each blood sample time point, which can be used in future, unspecified research. Study participants who decline donating blood to this biobank for future research can still participate in the clinical trial. Collected material in the biobank for future research can only be used in future research projects after approval from the Ethics Committee and approval from the trial research team. The material will be stored at the Department of Clinical Biochemistry, AUH, for 15 years. After this time point leftover material will be destroyed.

### **Sample size calculation and statistics**

An alpha (two-sided) of 0.05 and power ( $1 - \beta$ ) of 90 % have been applied for the sample size calculation. The primary endpoint is platelet aggregation measured by Multiplate®. From a previous study, the mean of the area under the curve for collagen-induced platelet aggregation was found to be 815 AU x min with standard deviation 130 AU x min [24]. We wish to detect a difference of at least 125 AU x min, which leads to inclusion of 23 patients in each of the two groups. We have chosen to include 30 patients in each group.

The difference in biochemical markers between groups over time will be tested using ANOVA models. The difference between groups at specific time points will be tested with the unpaired t-test for parametric data or the Wilcoxon rank-sum test for non-parametric data.

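### The primary endpoint names no time point and no primary test, so the 5% error rate assumed in the sample size calculation is not secured

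*Protocol*

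**What the plan says.** All of the following is in the protocol.

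- **Endpoint** (Sample size calculation and statistics): "The primary endpoint is platelet aggregation measured by Multiplate". The sentence gives no agonist, time or summary measure. Hypothesis 1, under Hypotheses, adds none.
- **Sizing** (same section): "An alpha (two-sided) of 0.05 and power" "of 90 % have been applied for the sample size calculation". The inputs are collagen only: "collagen-induced platelet aggregation was found to be 815 AU x min with standard deviation 130 AU x min", and "We wish to detect a difference of at least 125 AU x min". The result is 23 per group; 30 per group are planned.
- **Analysis** (same section): "The difference in biochemical markers between groups over time will be tested using ANOVA models". The next sentence adds unpaired t-tests, or Wilcoxon rank-sum tests for non-parametric data, at particular time points that it does not list. Platelet aggregation stands among the biochemical data under Outcomes, so both sentences apply to the primary endpoint.
- **Sampling** (Outcomes): five blood samples, two before the intervention and three after it: at 3 h, at 6 h, and at "06:30 AM on the 1st postoperative day".

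No order of testing and no multiplicity rule is given.

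**The concern.** The sample size corresponds to one t-test of one variable at one time. The endpoint sentence is wider than that, and the first analysis listed is a different test. At least four results could be offered as the primary one: the ANOVA, and a comparison at each of three times. Nothing in the protocol ranks them.

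Two things are at stake. If more than one result may carry the claim, the chance of a false claim for Hypothesis 1 exceeds the 5% used in planning. And if the results disagree, the choice between them could be made after the data are seen, with no text to show otherwise.

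**Working it through.** **Inputs.** From the protocol: two-sided alpha 0.05, power 90%, difference 125, SD 130, 23 calculated and 30 planned per group, three post-intervention times. Assumed: the correlation ρ between times, which the protocol does not give; equal correlation and equal variance at all three times; testing each time at 0.05.

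**1. The plan's own figure.** n = 2 × SD² × (z₀.₉₇₅ + z₀.₉₀)² / difference² = 2 × 130² × (1.960 + 1.282)² / 125² = 2 × 16,900 × 10.507 / 15,625 = 22.73, so 23 per group. This reproduces the protocol. The noncentral t version gives 24, a difference of approximation only. The figure belongs to a single two-group comparison.

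**2. Error if any of three time-point tests counts.** If independent: 1 − 0.95³ = 14.3%. With common correlation ρ and c = 1.960 the error is

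1 − ∫ φ(u) [Φ((c − √ρ·u)/√(1 − ρ)) − Φ((−c − √ρ·u)/√(1 − ρ))]³ du.

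The second column below evaluates this integral. The other columns come from 40,000 simulated null trials with 30 per group and the three post-intervention times. The simulation error is about √(0.15 × 0.85 / 40,000) = 0.2 percentage points.

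| ρ (assumed) | Three tests, integral | Three t-tests, simulated | plus ANOVA group-by-time | plus ANOVA group effect as well |
|---|---|---|---|---|
| 0 | 14.3% | 14.3% | 15.1% | 16.9% |
| 0.3 | 13.6% | 13.3% | 15.3% | 16.1% |
| 0.5 | 12.5% | 12.6% | 15.3% | 15.8% |
| 0.7 | 10.9% | 11.0% | 14.5% | 14.7% |
| 0.9 | 8.4% | 8.6% | 12.8% | 12.8% |

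Either ANOVA test used alone stays between 4.8% and 5.1%.

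**3. Power with 30 per group.** Noncentrality = 125 / (130 × √(2/30)) = 3.724 on 58 degrees of freedom.

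- One test at 0.05: 95.6%.
- One given time at 0.05/3 = 0.0167 (Bonferroni): 89.2%. Holm is never less powerful than Bonferroni, so this is a floor.
- For comparison, 23 per group at 0.0167: 77.6%.

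**The case against.** The strongest reply is that the protocol leaves the matter open and does not commit itself to an inflated procedure. The ANOVA is listed first and can be read as the overall test, with the time-point tests describing where a difference lies; on that reading the error stays near 5%. A statistical analysis plan that is not shown could also settle the ranking and any adjustment.

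Much of this stands, and it limits what may be claimed. A reader might infer that:

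- *every test is run at 0.05.* The protocol gives 0.05 for the sample size calculation only.
- *any significant result is enough to accept Hypothesis 1.* No section states such a rule, and the time points to be tested are not said to be all three.
- *several agonists multiply the error further.* Collagen is the only agonist named, and a second is never planned.
- *the t-test and the Wilcoxon test are two chances.* They are alternatives; the two competing kinds of test are the ANOVA and the time-point tests.
- *the trial is too small.* The 23 reproduces, and 30 per group nearly covers even a three-way Bonferroni split.

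The documents do not support any of these, so it cannot be said that the 5% rate is lost. What the reply does not remove is the gap itself. The protocol declares a primary endpoint, sizes the trial on a narrower variable, and lists competing tests of it. Which measurement at which time carries the primary claim is part of the endpoint's definition and belongs in the protocol; it is not a modelling detail to be left for later.

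**Conclusion.** The concern holds as a gap in the definition of the primary comparison. As written, the protocol does not identify the result that answers Hypothesis 1, so 5% is unsecured.

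The size is conditional. It is about 8% to 14% if the three post-intervention times are each tested at 0.05 and any success counts, and about 13% to 17% if the ANOVA tests count too. Both ranges rest on assumed correlations between 0.9 and 0 and on a decision rule that the protocol neither states nor excludes. With one pre-named test the rate is 5%.

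**What to change.** Before any results by group are seen, state that the primary endpoint is collagen-induced Multiplate AUC, tested once at two-sided 0.05 by one named comparison adjusted for the value in the second sample (taken at randomization). The comparison is one of:

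- **one post-intervention time with a fixed lag**, 3 h or 6 h, at the sponsor's choice. The third time is less suitable: it is set by the clock, and under Ethical considerations that sample may come from a central line or venipuncture instead of the arterial cannula. These reasons do not separate 3 h from 6 h.
- **one ANOVA group contrast**, written out in full. A contrast averaging the three times would dilute an effect of 125 present at only one of them to 125/3 = 41.7.

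Name the test as well, and call all other times and tests secondary. Alternatively, keep all three times as primary and apply Holm.

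**Cost.** A sentence or two and no extra patients. With one comparison, an effect seen only at another time no longer carries the primary claim. With Holm, power at a given time falls from 95.6% to no lower than about 89% with 30 per group. These power figures are for an unadjusted comparison at one time; the adjustment costs one degree of freedom, and any gain from it depends on a correlation that the protocol does not give.

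### The time-point comparisons leave out the two pre-intervention samples, and the ANOVA over time does not say how they enter; adjusting for the randomization sample would gain precision at no cost

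*Protocol*

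**What the plan says.** All references are to the Protocol.

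- **Samples (Outcomes).** Blood is drawn five times. The first draw is just before induction of anesthesia. The second is listed as "At randomization (intraoperatively"). The last three are at 3 h and 6 h after RIPC/sham and on the morning of the first postoperative day. Patients are randomized after induction and the later draws are timed from the intervention, so the first two samples precede it.
- **Analysis over time (Sample size calculation and statistics).** "The difference in biochemical markers between groups over time will be tested using ANOVA models". The text does not say which samples enter or what role the pre-intervention values play.
- **Analysis at single times (same section).** "The difference between groups at specific time points will be tested with the unpaired t-test for parametric data or the Wilcoxon rank-sum test" (the latter for non-parametric data). No baseline covariate or change from baseline is mentioned here or elsewhere in the protocol.
- **Sample size (same section).** "The primary endpoint is platelet aggregation measured by Multiplate". The collagen-induced area under the curve "was found to be 815 AU x min with standard deviation 130 AU x min [24", and the target difference is 125 AU x min. This gives 23 per group, and then: "We have chosen to include 30 patients in each group".

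**The concern.** An unpaired test on the 3 h, 6 h or day-1 value leaves in its error term all the between-patient spread that was there before the tourniquet was inflated. Eligibility does not restrict medication or co-morbidity, so lasting differences between patients in platelet aggregation are plausible, and the sample at randomization would capture part of them.

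Two things are at stake in a trial of 60 patients. The confidence interval for the effect is wider than the collected data allow. And if the groups happen to differ in platelet aggregation at randomization, part of that difference carries into the unadjusted result and cannot be told apart from an effect of RIPC.

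**Working it through.** **Inputs from the protocol:** two-sided alpha 0.05, power 90%, SD 130, target difference 125 AU x min, 30 per group. **Assumption:** the correlation r between the randomization value and a later value is not given; 0.3, 0.5 and 0.7 are shown. The SD is taken as 130 at every time.

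**1. The protocol's own figure.** n = 2 × (1.960 + 1.282)² × 130² / 125² = 22.7, so 23 per group. This matches. (The t-based version gives 23.7, which the chosen 30 covers.) It is a calculation for one unadjusted value per patient.

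**2. The unadjusted test at 30 per group.** SE = 130 × √(2/30) = 33.6. Power for 125 is 95.6% (t-based; 96.1% by normal approximation). The difference detectable with 90% power is 110.7, already below 125.

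**3. ANCOVA on one pre-intervention value.** Residual SD = 130 × √(1 − r²); SE and detectable difference shrink by the same factor. Effective n = 30 / (1 − r²).

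| | unadjusted | r = 0.3 | r = 0.5 | r = 0.7 |
|---|---|---|---|---|
| Residual SD | 130 | 124.0 | 112.6 | 92.8 |
| SE of the difference | 33.6 | 32.0 | 29.1 | 24.0 |
| Detectable with 90% power | 111 | 106 | 96 | 79 |
| Effective n per group | 30 | 33 | 40 | 59 |
| Fall in variance (r²) | – | 9% | 25% | 49% |

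These figures ignore the small cost of estimating the slope. With 60 patients this raises the variance on average by a factor of 1 + 1/(60 − 4) = 1.018, or about 1% on the SE. Even at r = 0 the SE would only go from 33.6 to 33.6 × √1.018 = 33.9.

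**4. Chance imbalance at randomization.** The baseline group difference has the same SE, 33.6. P(|difference| ≥ 50) = 2 × [1 − Φ(50/33.6)] = 0.136, about 14% of trials. With equal SDs, a baseline difference d shifts the expected later difference by r × d. For d = 50 this is 15, 25 and 35 AU x min, or 12%, 20% and 28% of the 125 target.

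**5. The ANOVA over time.** If all five samples enter as time levels, the group main effect averages over two times at which no effect is possible. A constant effect of 125 at the last three samples would appear as 125 × 3/5 = 75. A group-by-time term avoids this, but it is an overall test and does not itself give the effect at 3 h, 6 h or day 1. For those times the stated method remains the unadjusted test.

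**The case against.** The strongest objection is that the sentence just before the quoted one plans ANOVA models over time. A repeated-measures model with a group-by-time term that includes the first two samples would use the pre-intervention values and remove stable between-patient spread. This stands: a reader might infer that every group comparison ignores baseline, and the protocol does not support that. It does not say which samples enter the ANOVA, nor whether the ANOVA or the time-point tests are primary. If the latter only follow up the ANOVA, less hangs on them.

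Three further points also limit the concern.

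- A reader might infer that the unadjusted estimate is biased, or that a baseline imbalance passes into it in full. Neither holds. Under randomization the estimate is unbiased on average, the chance variation is already in the SE of 33.6, and an imbalance carries over only in proportion to r.
- A reader might infer that the trial is underpowered without adjustment. On the protocol's own inputs it is not.
- The gain depends on an assumed r. The samples span anesthesia, resection, reconstruction and the following morning, so r may be low. At 0.3 the detectable difference moves only from 111 to 106.

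Two replies do not succeed. One is that baseline adjustment can be left to a SAP: the protocol itself names an unadjusted test, so a SAP specifying ANCOVA would depart from it. The other is that a t-test or rank-sum test on change from baseline would serve. The SD of a change is 130 × √(2 − 2r), that is 153.8, 130.0 and 100.7 at r = 0.3, 0.5 and 0.7. This is worse than, equal to and better than the raw value, and above the ANCOVA residual SD in every case.

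**Conclusion.** The point holds as a matter of precision. The single-time-point tests use neither of two pre-intervention values that every patient provides, and the role of those values in the ANOVA is left open. The planned tests are valid. With SD 130 and 30 per group they have about 95.6% power for 125 AU x min, so the change repairs neither bias nor a power shortfall.

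The gain is a fall in SE from 33.6 to between 32.0 (r = 0.3) and 24.0 (r = 0.7), with less exposure to an imbalance of 50 AU x min or more, which about one trial in seven would show. That chance and the SEs rest on the protocol's SD of 130 holding at each time; the gain also rests on the assumed r. That adjustment is valid, and costs about 1% in SE at worst, depends on neither.

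**What to change.** In Sample size calculation and statistics:

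1. Replace the t-test/Wilcoxon sentence with: *Group differences at 3 h, 6 h and the first postoperative day are estimated by ANCOVA with the sample-2 (randomization) value of the same marker as covariate; skewed markers are log-transformed and reported as ratios.*
2. Add to the ANOVA sentence: *The model over time includes samples 3 to 5 only, with the same baseline covariate.*
3. Keep the unadjusted test as a sensitivity analysis for the primary endpoint.

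The cost is two or three sentences. No extra blood, assays or patients are needed, and the sample size can stay as it is.
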